**Fig. 1 Fig1:**
[figure not shown]
The Standard Gamble experiment to be performed with parents assessing three health states related to dental caries in their child’s primary molars

### Analytical methods

The economic evaluations will be considered intention-to-treat analyses using data collected after 2 years, as previously described. In the case of missing data, we will investigate their nature and choose the most appropriate method to handle the missing data, e.g., multiple imputations. Imputations will consider health and economic outcomes and the possible relationship between them and other pertinent covariates. When new operative treatments have been performed externally to the research, the same strategy used for missing data will be used for cost estimation.

Cox regression model with shared frailty will be used to compare the need for a new intervention. The health effects listed above will be compared between groups using the most appropriate statistical test, depending on data distribution. Given the usual right-skewed distribution of cost data, we will use the bootstrapping quantile regression to compare the total costs of the diagnostic strategies [28]. Bootstrapping replications will be set at 1000, and a fixed seed will be determined. We will use the software Stata13 (StataCorp LP, Texas, USA) and set a 5% significance level for these analyses.

We will work with the difference between the strategies both regarding the inputs (∆costs: CARS costs − FDI costs) and outputs (∆effects: CARS effects − FDI effects) since the focus of this series of economic evaluations is the economic impact of using the minimally invasive strategy (based on CARS) instead of the conventional strategy (based on FDI criteria) for managing dental restorations. Bootstrap confidence intervals will be calculated for each parameter considering the costs, effects, incremental costs, and incremental effects [29].

Deterministic one-way sensitivity analysis will be conducted for CEAs and CUA to assess the quantitative relationship among estimates in parameters that could perform differently in a distinct scenario, such as costs, discount rate, and effects. In these analyses, we will also test the influence of different baseline conditions as covariates associated with the effects and costs [30], checking the possibility of extrapolating data from this single trial to a broader population. The results will be demonstrated in a tornado diagram.

Additionally, a Bayesian approach will be used to explore uncertainties on the same parameters. By adopting this approach, we will describe the probabilities around the actual values obtained in this study [31–33]. The data distribution of costs and effects will be checked using XLSTAT Premium 2021.3.1 (Addinsoft, Paris, France), and, based on that distribution, Monte-Carlo simulations (× 10,000) will be generated to be plotted in a cost-effectiveness plane (CE plane). The proportion of points in each quadrant of the CE plane will be calculated, and the location of points will also be assessed visually. We will calculate the incremental net benefit using the following equation:

Incremental Net Benefit = Incremental Effect × Ceiling Ratio − Incremental Cost, being value 1 for a positive coefficient and 0 for a negative coefficient value. Thus, for the interpretation, if the difference is higher than zero (the value 1), it means that for one additional unit of effectiveness, the incremental cost is below the Ceiling Ratio (the maximum value that decision-makers are willing to pay). If the difference is less than zero (the value 0), the incremental cost of each additional unit of effectiveness is above the Ceiling Ratio [34]. Finally, acceptability curves will be plotted for each effect using the incremental net benefit framework and assuming different ceiling ratios to check the uncertainties around threshold points.

Subgroup analyses considering age (3 to 6 vs 7 to 10 years) and patients’ caries experience (≤ 3 vs > 3 restorations) will also be conducted.

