**Methods:**

A trial-based economic evaluation will be conducted, including three cost-effectiveness analyses (CEA) and one cost-utility analysis (CUA). These analyses will be based on the main trial (CARDEC-03/NCT03520309), in which children aged 3 to 10 were included and randomized to one of the diagnostic strategies (based on FDI or CARS). An examiner will assess children’s restorations using the randomized strategy, and treatment will be recommended according to the same criteria. The time horizon for this study is 2 years, and we will adopt the societal perspective. The average costs per child for 24 months will be calculated. Three different cost-effectiveness analyses (CEA) will be performed. For CEAs, the effects will be the number of operative interventions (primary CEA analysis), the time to these new interventions, the percentage of patients who did not need new interventions in the follow-up, and changes in children’s oral health-related quality of life (secondary analyses). For CUA, the effect will be tooth-related quality-adjusted life years (QALYs). Intention-to-treat analyses will be conducted. Finally, we will assess the difference when using the minimally invasive strategy for each health effect (∆effect) compared to the conventional strategy (based on FDI) as the reference strategy. The same will be calculated for related costs (∆cost). The discount rate of 5% will be applied for costs and effects. We will perform deterministic and probabilistic sensitivity analyses to handle uncertainties. The net benefit will be calculated, and acceptability curves plotted using different willingness-to-pay thresholds. Using Markov models, a longer-term economic evaluation will be carried out with trial results extrapolated over a primary tooth lifetime horizon.

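### The named between-arm test of total costs targets an unspecified quantile, whereas the economic evaluation needs the difference in mean cost per child

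*Protocol article*

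**What the plan says.** All of the following is from the protocol article.

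- **Cost comparison (Analytical methods).** The reason given is "Given the usual right-skewed distribution of cost data"; the method is that "we will use the bootstrapping quantile regression to compare the total costs of the diagnostic strategies". No quantile is named. The same paragraph adds "Bootstrapping replications will be set at 1000, and a fixed seed will be determined" and says the team will "set a 5% significance level for these analyses".
- **Cost summary (Abstract, Methods).** "The average costs per child for 24 months will be calculated".
- **Incremental cost (Analytical methods).** It is defined as a difference between arms ("costs: CARS costs − FDI costs"), without saying which summary of cost is differenced.
- **Interval estimates (Analytical methods).** "Bootstrap confidence intervals will be calculated for each parameter considering the costs, effects, incremental costs, and incremental effects". The statistic to be bootstrapped is not stated.
- **Decision quantity (Analytical methods).** "Incremental Net Benefit = Incremental Effect × Ceiling Ratio − Incremental Cost". The cost-effectiveness plane comes from Monte-Carlo draws based on the observed cost and effect distributions, and acceptability curves follow from the net benefit.

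**The concern.** Right skew makes it harder to estimate the uncertainty of a mean. That is a reason to bootstrap the mean or to model it with a suitable error distribution. It does not change which parameter the decision needs. Whether one strategy allocates resources more efficiently depends on total spend, and total spend is the mean times the number of children. Medians and other quantiles do not have this property. Bootstrapping a quantile regression only supplies standard errors for the quantile coefficient; it does not turn that coefficient into a mean difference.

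At stake is the coherence of the cost results. The paper could report no significant cost difference beside a clear mean incremental cost, or a significant difference where mean costs are equal. A reader could not tell which to believe, and the article does not say that the two address different parameters.

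**Working it through.** The article gives no cost mean, median, standard deviation or power figure for the cost comparison, so there is no stated figure to reproduce. The check sets the statements side by side and then illustrates, with assumed inputs, what can happen.

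**1. Target of each component**

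| Component | What is stated | Target |
|---|---|---|
| Between-arm cost test, 5% level | bootstrapped quantile regression | a quantile, unnamed |
| Cost summary | average cost per child over 24 months | arithmetic mean |
| Incremental cost and its bootstrap interval | CARS minus FDI | not stated; the mean is what is needed |
| Net benefit | incremental effect × ceiling ratio − incremental cost | needs the mean |

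The first row differs from the others, and no sentence reconciles them.

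**2. Mean and median contrasts with log-normal costs (assumed)**

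For log-SD s, mean = median × exp(s²/2).

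- *Equal medians of 100, log-SD 0.5 and 0.8.* Means are 100 × exp(0.125) = 113.3 and 100 × exp(0.32) = 137.7. The median difference is 0 and the mean difference is 24.4. With log-SD 0.6 and 1.0 the mean difference is 45.2; with 0.8 and 1.0 it is 27.2.
- *Equal means of 100, log-SD 0.5 and 0.8.* Medians are 100 × exp(−0.125) = 88.2 and 100 × exp(−0.32) = 72.6. The mean difference is 0 and the median difference is 88.2 − 72.6 = 15.6 in absolute value.
- *Equal log-SDs.* The ratio of medians equals the ratio of means, so the two contrasts agree in direction. With medians both 100, both differences are 0.

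**3. A tail difference (assumed)**

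Base cost is log-normal with median 100 and log-SD 0.3. A 300-unit reintervention is added for 10% of CARS children and 20% of FDI children. The true mean difference is 300 × (0.10 − 0.20) = −30.0. Simulated quantile differences, CARS minus FDI, with 1,000,000 draws per arm:

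| Contrast | Difference |
|---|---|
| Mean | −30.0 |
| 25th percentile | −2.6 |
| Median | −5.8 |
| 75th percentile | −24.9 |

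The median contrast recovers 5.8 / 30.0 = 19% of the mean difference and the 75th percentile 24.9 / 30.0 = 83%. The choice of quantile, which the article leaves open, therefore largely decides what the test sees.

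**4. What follows**

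Under skew, a quantile contrast can understate a mean difference, miss it, or show a difference where the means are equal. It can also agree in direction when the two distributions have the same shape. Which case applies here depends on data that the article does not contain.

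**The case against.** The strongest reply is that the decision analysis is described separately. Quantile regression is named only for comparing total costs. The incremental cost, its bootstrap interval, the cost-effectiveness plane and the net benefit come in later paragraphs, and nothing feeds the quantile coefficient into them. The abstract speaks of average costs, so these outputs may well be mean-based. This stands, and it rules out some stronger readings that a reader might infer:

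- *That the net benefit or the cost-effectiveness results will use medians, or that no mean cost will be estimated.* The article says neither.
- *That the quantile test is the headline cost result.* Nothing calls it primary or makes a conclusion depend on its p-value.
- *That the cost difference comes from a late tail of children needing reintervention.* The Background reports that replacements were indicated more often under FDI at baseline, and the Discussion expects added costs from the first treatment plan. Costs may therefore shift across many children.
- *That a known fraction of the true difference is lost.* The illustrations rest on assumed distributions, and a figure for the median presumes a quantile that the article does not name.

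It can also be said that details may sit in the supplements, in an analysis plan not shown, or in the reference cited for the method. That may cover the undefined incremental cost. It does not cover the named test: the article presents itself as the health economic analysis plan, and it states the method and the reason for it.

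**Conclusion.** The point holds in a limited form. The only method named for testing total costs between arms estimates a quantile difference, and skew does not justify that change of target. The evaluation needs the difference in arithmetic means. The article neither defines incremental cost as that difference nor shows the quantile result entering net benefit. The established defect is thus a cost test that addresses a different quantity and could conflict, in either direction, with a mean-based incremental cost reported beside it.

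Its size in this trial cannot be computed. The illustrative contrasts show only what is possible, and they rest entirely on assumed cost distributions. This should be fixed, but it does not by itself invalidate the planned net-benefit analysis.

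**What to change.** In Analytical methods:

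1. Define incremental cost as the difference in arithmetic mean cost per child, CARS minus FDI, over 24 months.
2. Make the between-arm cost comparison that mean difference, with a bootstrap interval that resamples children within arm. A mean-based GLM, for example gamma with log link and standardised predictions, is an acceptable alternative.
3. State that the same estimate enters the net benefit.
4. Keep quantile regression as a description of the cost distribution, and name the quantiles.

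The cost is a few sentences and a few lines of Stata code. The bootstrap is already planned and no new data are needed. The downside is that intervals for the mean may be wider when the cost tail is heavy; that width reflects real uncertainty about the quantity the decision depends on.

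### As written, the CE plane and acceptability curves come from simulation of the cost and effect data, with no scaling to uncertainty in the mean increments and no stated pairing of cost with effect

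*Protocol article*

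**What the plan says.** Under Analytical methods, the probabilistic step is introduced with the words "a Bayesian approach will be used to explore uncertainties on the same parameters", and its purpose is given as "we will describe the probabilities around the actual values obtained in this study". The mechanism is then stated: "The data distribution of costs and effects will be checked using XLSTAT Premium 2021.3.1 (Addinsoft, Paris, France), and, based on that distribution, Monte-Carlo simulations", numbering "10,000) will be generated to be plotted in a cost-effectiveness plane (CE plane"). The output is read off the points: "The proportion of points in each quadrant of the CE plane will be calculated". Net benefit is scored by sign: "Incremental Net Benefit = Incremental Effect × Ceiling Ratio − Incremental Cost, being value 1 for a positive coefficient and 0 for a negative coefficient value". Acceptability curves are built on that net-benefit framework over a range of ceiling ratios.

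The same section plans a bootstrap ("Bootstrapping replications will be set at 1000, and a fixed seed will be determined") for the quantile regression of costs, and bootstrap confidence intervals for costs, effects and their increments. It does not say that either supplies the points in the plane or the curves.

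The section on modelling for the primary tooth lifetime horizon reuses the probabilistic strategy of the trial-based analysis.

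**The concern.** An acceptability curve should give the probability that the mean net benefit is positive, given what the trial has shown. That needs draws from the uncertainty distribution of the mean increments, whose variance shrinks as n grows. Draws from the distribution of the data have the spread of individual children, which does not shrink. Counting such points answers another question: roughly, how often one random CARS child has a better net benefit than one random FDI child.

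The text names no standard error, no sampling distribution of a mean and no posterior. The Bayesian label does not fill the gap, because no prior or posterior for the means is described. Elsewhere in the section the distribution of data means the spread of observations: it governs the choice of test, and costs are called right-skewed. The literal reading is therefore a natural one.

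A second gap is that net benefit combines cost and effect, so its variance depends on their covariance. A relationship between the two is mentioned only for imputation.

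Quadrant shares and acceptability curves are the plan's main statement of decision uncertainty. If they are built from child-level draws, a clearly favourable or unfavourable result would look close to a coin toss, in the trial analysis and again in the lifetime model.

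**Working it through.** The article gives no probability, SD, correlation or main-trial sample size on this point, so there is no stated figure to reproduce. Every numeric input below is an assumption, except the 10,000 draws and the net-benefit formula.

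**1. General effect of omitting the division by n.** Assume n = 50 to 150 children per arm, equal arms and a normal approximation.

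- Mean-level draws: P(INB > 0) = Φ(z), where z is the mean net benefit divided by its standard error.
- Child-level draws: the SD is √n times larger, so P = Φ(z/√n).
- √50 = 7.1 and √150 = 12.2, hence 7 to 12 times.

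| z | mean-level | child-level, n = 50 | child-level, n = 150 |
|---|---|---|---|
| 2 | 0.977 | Φ(0.283) = 0.61 | Φ(0.163) = 0.56 |
| 3 | 0.999 | Φ(0.424) = 0.66 | Φ(0.245) = 0.60 |

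**2. Worked example with both issues.** Effect is counted as interventions avoided. Assume ΔE = 0.25, ΔC = −20, child-level SDs sE = 1.0 and sC = 80, ceiling ratio λ = 100, and correlation ρ = −0.4 between interventions avoided and cost.

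- INB = λΔE − ΔC = 25 + 20 = 45.
- Child-level variance = 2(λ²sE² + sC² − 2ρλ·sE·sC). Mean-level variance is this divided by n.
- With ρ = −0.4: 2(10,000 + 6,400 + 6,400) = 45,600, SD 213.5.
- With ρ = 0: 2(10,000 + 6,400) = 32,800, SD 181.1.

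| P(INB > 0) | n = 50 | n = 100 | n = 150 |
|---|---|---|---|
| means, correlation kept | 0.932 | 0.982 | 0.995 |
| means, correlation ignored | 0.961 | 0.994 | 0.999 |
| child-level, correlation kept | 0.583 | 0.583 | 0.583 |
| child-level, correlation ignored | 0.598 | 0.598 | 0.598 |

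The child-level rows do not change with n, so they cannot be expressing how much the trial has taught us.

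**3. Check with skewed data.** Gamma costs and Poisson intervention counts, n = 100, λ = 100, 10,000 independent draws: 0.614 at child level against 0.994 for means. The normal approximation with ρ = 0 gives 0.598 and 0.994, so skewness does not change the picture here.

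**4. Correlation alone, at mean level.** With n = 50 and λ = 100:

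- at ρ = −0.7, ignoring the correlation turns 0.912 into 0.961, a shift of about 0.05;
- at ρ = +0.4, it turns 0.988 into 0.961, a shift the other way;
- at λ = 0 the covariance term vanishes and nothing changes.

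If the two components of net benefit have equal SD and the size of the negative correlation is 0.4 to 0.8, independent draws understate the SD by √1.4 = 1.18 to √1.8 = 1.34.

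**The case against.** The best defence is that the sentence is short and need not mean child-level draws. Its stated target is uncertainty on the same parameters, and just before it the section uses that word for costs, effects and their increments, with bootstrap intervals. Checking the data distribution may then mean only choosing a family, such as a gamma for skewed costs, to be set by a mean and a standard error. This stands as a possible reading. A reader might infer that the acceptability curves are simply wrong; the article does not support that, and they go wrong only if the step is carried out literally.

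Two further inferences also go beyond the text. One is that costs and effects are drawn from separately fitted distributions. The article never says so; it is silent on whether the draws are joint. The other is that the cost-effect correlation must be strong because every counted intervention generates a cost. Under Health outcomes, an event is a need identified by a blinded assessor using a different approach from the randomized strategies, or an episode of pain. Under Comparators, treatment is planned by another examiner following the randomized strategy, and it is the care given that is costed. The primary effect also counts only interventions after the baseline assessment, whereas the Discussion expects baseline treatment to add cost. A link is likely, but its strength and sign are unknown.

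It can also be said that the planned bootstrap already covers mean-level uncertainty. It does so for the confidence intervals. The Monte-Carlo step, however, is presented as an addition with its own software and number of draws, and nothing carries the bootstrap into the plane or the curves.

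Finally, an article may leave implementation to supplements that are not shown. That would excuse silence about scaling, but here the article does state the source of the draws, and the source it states is the data distribution.

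**Conclusion.** The point holds conditionally. As written, the CE-plane points, and with them the quadrant shares and acceptability curves, are simulated from the data distribution, with no provision for uncertainty in the mean increments. Followed literally, this inflates the SD of net benefit by about root n and pulls probabilities toward 0.5: from 0.977 to about 0.61 to 0.56 at 2 standard errors, for an assumed 50 to 150 children per arm. The lifetime model inherits the approach.

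The absence of any stated pairing is secondary. In the example it moved the mean-level probability by at most about 0.05, with a direction set by the sign of the correlation.

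The sizes rest on assumed n, SDs, correlation and ceiling ratio. The direction of the main distortion rests only on the draws being made at child level. In the worked example the two readings give roughly 0.6 and 0.93 to 0.995. A plan published for reproducibility should not leave that choice open.

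**What to change.** State that the CE plane, quadrant shares and acceptability curves are generated from **mean** incremental costs and **mean** incremental effects, simulated jointly. Either of two routes would do:

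- resample children with replacement within each arm, keeping each child's cost and effect together, and compute the mean increments in every replicate; this extends the bootstrap already planned;
- draw the means from a bivariate sampling distribution with the estimated standard errors and covariance.

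Apply the same rule to trial-derived parameters in the lifetime model: distributions set by the uncertainty of the estimate, not by the spread of the data. If the Bayesian label is kept, name the prior and the posterior quantity that is sampled. Using more than 1,000 bootstrap replicates for the curves, say 5,000 to 10,000, is a preference and corrects no error.

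The cost is a few sentences and analysis code. No further data are needed, and the article reports that the economic evaluation had not begun.

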### Study design

A trial-based economic evaluation will be conducted (piggyback approach), including three cost-effectiveness analyses (CEA)—different health effects—and a cost-utility analysis (CUA). The clinical trial investigating the diagnostic strategy for restorations assessment is the third diagnostic study conducted by the CARDEC collaborative group at the School of Dentistry of the University of São Paulo (São Paulo, Brazil). The CARDEC-03 trial is a two-arm, parallel-group, patient-randomized controlled trial aiming to assess which diagnostic strategies (based on FDI criteria or CARS) leads to fewer new interventions in restored primary teeth during 2 years of follow-up. Further details regarding the trial have been published in the study protocol [7].

The strategy based on the FDI criteria will be acknowledged as the reference strategy for assessing the restorations. However, recognize there is no robust evidence supporting this assumption. Despite this, a reference strategy for economic evaluation must be assumed. Considering that the CARS strategy is associated with a less interventionist approach, we will consider it as the new strategy. Moreover, FDI criteria were first proposed and appointed by experts as the standard criteria for restorations’ assessment [16, 17].

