### Health outcomes

Three health effects will be considered for different CEAs to bring different perspectives when decision-making. The primary health effect considered will be the number of new operative interventions per child after the baseline assessment. Other endpoints were set as secondary health effects: the time to the new operative interventions (survival), the percentage of children who did not need new operative interventions, and the relevant change in the Oral Health-Related Quality of Life (OHRQoL) scores (Table 2).

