**Table 2 Tab2:**
[figure not shown]
Summary of health outcomes (health effects) used in economic evaluations

*95%CI** bootstrap-adjusted confidence interval at 95%

For the first health outcomes (related to new operative interventions), we will assess the children for 24 months, following them each 6 months. The cumulative result will be accumulated for 24 months when computing the number of events (new interventions) and the time to an event during this period. The restorations will be evaluated by an examiner ([name]), blinded to the diagnostic strategy. At this assessment, surfaces were scored according to the restoration integrity and occurrence of caries, determining the need (or not) of repair, replacement, or other possible new interventions [22, 23] (Table 2). At this stage, the idea was to use an external assessor using a different approach (from those interventions under comparison and randomized) not to bias the outcome assessment. Based on this assessment, new interventions (events) will be considered when any need for restoration repair or replacement is identified, any presence of secondary caries lesion exposing dentin is detected, any need for extension of the existing restoration or endodontic treatment is required (due to caries or tooth fracture), and/or any episode of pain is reported (Table 2).

The OHRQoL will be assessed using the Brazilian version of the Early Childhood Health Impact Scale (B-ECOHIS) [24]. This questionnaire is answered by parents as a proxy of the child’s OHRQoL and is a valid measure for children [25]. Although the ECOHIS has been proposed for pre-school children [26], it was chosen to measure effectiveness in the entire sample, comprising children from 3 to 9 years old. The questionnaire was answered in the baseline and will be answered at 24-month follow-up completion. The difference between the ECOHIS final and baseline scores will be calculated. The change in ECOHIS scores will be classified according to the minimal important difference calculated [25].

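### As printed, the net-benefit rule gives the primary effect the wrong sign: avoided interventions count against CARS

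*Protocol article*

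**What the plan says.** Four statements in the Protocol article bear on the point.

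- **Primary effect.** Health outcomes: "The primary health effect considered will be the number of new operative interventions per child after the baseline assessment". The text below Table 2 in that section defines the events: "new interventions (events) will be considered when any need for restoration repair or replacement is identified", and likewise for caries exposing dentin, extension of the restoration, endodontic treatment or pain. Study design gives the favourable direction: the trial asks which strategy "leads to fewer new interventions in restored primary teeth during 2 years of follow-up".
- **Increment.** Analytical methods sets the "outputs (∆effects: CARS effects − FDI effects", and costs in the same direction. It makes no exception for effects where lower is better.
- **Net benefit.** Analytical methods gives the formula "Incremental Net Benefit = Incremental Effect × Ceiling Ratio − Incremental Cost". Its scoring clause, which starts at the last term of that formula, reads "Incremental Cost, being value 1 for a positive coefficient and 0 for a negative coefficient value". The same paragraph says that acceptability curves will use this framework for each effect, so the primary count is included.
- **Interpretation.** Analytical methods explains a positive result in these words: "if the difference is higher than zero (the value 1), it means that for one additional unit of effectiveness, the incremental cost is below", which sets the cost of each unit against the ceiling ratio.

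The section on modelling for the primary tooth lifetime horizon carries the same deterministic and probabilistic strategies into the Markov model. The Discussion part of the abstract hypothesises more replacements, more reinterventions and higher costs under FDI.

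**The concern.** The net-benefit formula works only if a larger effect is a gain, because it pays the ceiling ratio for each extra unit. Here a unit of the primary effect is a repair, a replacement, an endodontic treatment or a similar unfavourable event. With the increment taken as CARS minus FDI, success for CARS gives a negative ∆E, and the formula charges CARS for it. The more a decision-maker is willing to pay to avoid an intervention, the worse CARS would look.

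At stake are the net benefit and the acceptability curve of the primary cost-effectiveness analysis, and their counterparts in the lifetime model if the same effect is used there. The Background says that publishing the plan guards against selective reporting and unplanned analyses. A sign reversed after the results are known is a change of that kind, so the direction should be fixed beforehand.

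**Working it through.** The article states no ∆E, ∆C or ceiling ratio, so there is no published figure to reproduce. The sign argument needs none. The numerical illustrations use assumed values.

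**Sign argument.** Write λ for the ceiling ratio, ∆E for the CARS minus FDI count and ∆C for the CARS minus FDI cost.

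- As printed: INB = λ∆E − ∆C.
- Sign corrected (interventions avoided): INB = λ(−∆E) − ∆C.

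Suppose CARS has fewer interventions, so ∆E < 0. The printed rule becomes INB = −λ|∆E| − ∆C.

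1. If ∆C ≥ 0, INB is negative for every λ > 0.
2. If ∆C < 0, INB = |∆C| − λ|∆E|. This is positive only while λ < |∆C|/|∆E|. The corrected form, λ|∆E| + |∆C|, is positive at every λ.
3. As λ grows, the printed acceptability curve tends to P(∆E > 0), the probability that CARS has more interventions.

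**Illustration A (assumed).** ∆E has mean −0.4 and SE 0.15; ∆C has mean −20 and SE 30; the correlation is 0.6; the distribution is bivariate normal. The covariance is 0.6 × 0.15 × 30 = 2.7.

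- Printed: mean = −0.4λ + 20; variance = 0.0225λ² + 900 − 5.4λ.
- Corrected: mean = 0.4λ + 20; variance = 0.0225λ² + 900 + 5.4λ.
- P(INB > 0) = Φ(mean/SD).

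| λ | Printed mean / SD | P | Corrected mean / SD | P |
|---|---|---|---|---|
| 0 | 20 / 30.0 | 0.75 | 20 / 30.0 | 0.75 |
| 50 | 0 / 26.2 | 0.50 | 40 / 35.0 | 0.87 |
| 100 | −20 / 24.2 | 0.20 | 60 / 40.8 | 0.93 |
| 200 | −60 / 26.8 | 0.01 | 100 / 53.7 | 0.97 |

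The printed mean changes sign at λ = 20/0.4 = 50, as step 2 predicts.

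**Illustration B (assumed, varying the cost difference).** ∆E has mean −0.3 and SD 0.1; ∆C has SD 20; the two are independent. At λ = 200 the SD of INB is √(20² + 20²) = 28.3.

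| Mean ∆C | Printed mean | P | Corrected mean | P |
|---|---|---|---|---|
| −30 | −30 | 0.14 | 90 | above 0.99 |
| 0 | −60 | 0.02 | 60 | 0.98 |
| +30 | −90 | below 0.01 | 30 | 0.86 |

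The reversal appears whether CARS is cheaper, equal in cost or dearer.

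**Interpretation sentence.** From λ∆E − ∆C > 0, dividing by ∆E gives ∆C/∆E < λ only if ∆E > 0. If ∆E < 0 the inequality turns round, ∆C/∆E > λ. For a properly oriented effect with ∆E < 0 and ∆C < 0, a positive INB means that the saving per unit forgone exceeds the ceiling.

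**The case against.** The strongest objection is that the article may not show the whole rule. The content of Table 2, which summarises the health effects, and the supplements are not visible, and one of them could code the primary effect as a reduction. The reference to an additional unit of effectiveness also suggests that the authors had in mind an effect where more is better. This limits what can be said about the full plan. It does not reconcile the printed rules, since the visible text consistently calls the effect a number of new interventions.

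A reader might also draw stronger conclusions, which the documents do not support.

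- **That CARS loses at every ceiling.** If CARS is also cheaper, the printed INB stays positive below |∆C|/|∆E|.
- **That every avoided intervention lowers net benefit outright.** This is true only with costs held fixed. Costs and resources micro-costs materials, staff time and family time, so an avoided intervention also reduces ∆C. The printed INB then changes by the cost saved minus λ.
- **That the quadrant shares of the cost-effectiveness plane are miscalculated.** Analytical methods attaches no favourable label to any quadrant. The plane is mirrored, and misleads only if conventional labels are applied.
- **That the OHRQoL effect has the same error.** The text below Table 2 says "The difference between the ECOHIS final and baseline scores will be calculated", but then classifies the change by the minimal important difference. It does not say which category enters the analysis, and the direction of the scale would have to be assumed.

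The fault in the interpretation sentence is one of wording. The curves rest on the sign of INB, not on that sentence.

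**Conclusion.** The concern holds for the primary effect as the rules are printed. The direction of the count, the direction of the increment and the net-benefit formula cannot all stand together. The error reaches the primary net benefit and acceptability curve, and can reverse the conclusion even when CARS is both cheaper and needs fewer interventions.

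The sign conclusion rests on the visible text alone. Its size depends on unknown inputs: in the first illustration the loss in P(INB > 0) is nil at a ceiling of 0 and 0.96 at 200. Time to intervention, the percentage of children free of intervention and tooth-related QALYs already run in the favourable direction, so the formula has the right sign for them. No error is shown for the OHRQoL effect.

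**What to change.** 1. Define the primary effect as interventions avoided (FDI count minus CARS count) for net benefit, the cost-effectiveness plane and the acceptability curve, in the trial-based analysis and in the lifetime model wherever this effect is used.
2. Label the quadrants of the cost-effectiveness plane to match.
3. Leave time to intervention, percentage intervention-free and tooth-related QALYs as CARS minus FDI.
4. State how the OHRQoL change is coded, and orient it so that higher means improvement if it is not already.
5. Replace the interpretation sentence with a statement that INB above zero means CARS is cost-effective at that ceiling ratio.

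If Table 2 or a supplement already reverses the count, say so in Analytical methods. The change is to wording only and needs no new data or patients. The article states that the economic evaluation had not begun.
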